### Statistical methods and analysis

Analyses of differences in the results between the two interventions will be undertaken both according to intention-to-treat principles and per protocol. Descriptive statistics and standard statistical tools (such as t-tests and chi-square tests) will be used to compare the baseline measurements of the treatment arms.

### Outcome assessment and evaluation

Cox proportional hazard models will be used to analyze the time until stable/sustainable RTW. Analyses will be performed for both full-time and part-time RTW. If there is an imbalance in any prognostic factors for RTW and this factor is strongly correlated with the RTW outcome, analyses of differences in RTW between the two clinics will be adjusted for prognostic dissimilarities if we have sufficient power [69]. To determine the probability of RTW, sick leave, other benefits, or disability pension, a multistate model can be established [70]. This model can determine whether there are differences in the patterns of RTW if differences in the results are discovered in the overall analyses. Since the primary outcome data are based on complete registry data, missing data should not be a problem.

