Several nonmodifiable prognostic factors for RTW that may influence work participation and the success of the interventions have also been identified. These factors include older age, lower educational level; lower socioeconomic status; and greater sick leave history [42], comorbidities [43], childhood adversities [44], and other life events [45]. Additionally, employment status and partial sick leave at baseline of the intervention [46] and timing of the intervention may also influence RTW [47].

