### Limitations of the study

A design with a randomized clinical trial is the preferred design to examine the study questions. This project started as a randomized clinical trial, but due to recruitment problems, it was not feasible to carry through. We stopped recruiting when we had reached approximately 80 participants and decided to change the design. These two randomized arms will be analyzed and reported separately as a pilot study. We do not have enough power in the statistical analyzes to evaluate whether there are any significant differences in effect between the two interventions.

With the two nonrandomized arms described in this article, we will not be able to evaluate whether there are any significant differences in effect between the two interventions, and we will not be able to eliminate the bias associated with differences in the referral of patients to the two clinics. However, interviews with nearly 40 participants, 4 times during a year from the randomized part of the study, will support us with valuable information regarding their reception of the interventions and mechanisms that influence their RTW process.

We know from interviews with participants that there is a bias associated with the referral of patients to the clinics due to patient preferences and possibilities. Some prefer the outpatient program because they can ensure their ability to fulfill family or work obligations or because they are not able to stay away from home for several weeks. On the other hand, some prefer the inpatient program because they can disconnect from family or work for a period.

Those who agree to participate in the study and those who decline may also differ in many unpredictable ways that we are not able to address with the current study design. However, we will look for any selection bias by comparing the demographic statistics and known predictors of RTW among those who agree to participate. The RTW rates in the study will also be compared with national RTW data from an established quality registry for occupational rehabilitation. We also plan to draw a matched group from the NAV registry representing those who receive treatment as usual and to compare RTW rates for this group with the results from the participating clinics.

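### Adjustment of the non-randomised clinic comparison depends on observed imbalance, correlation with RTW and power, so measured confounding can stay in the main result

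*Protocol article*

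**What the plan says.** Under Outcome assessment and evaluation, adjustment has three conditions. The first two are "If there is an imbalance in any prognostic factors for RTW and this factor is strongly correlated with the RTW outcome". The third follows in the same sentence: "analyses of differences in RTW between the two clinics will be adjusted for prognostic dissimilarities if we have sufficient power". The article does not say what counts as an imbalance, a strong correlation or sufficient power. Statistical methods and analysis says that "standard statistical tools (such as t-tests and chi-square tests) will be used to compare the baseline measurements of the treatment arms".

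Limitations of the study says that the randomised trial was abandoned and that the arms described here are non-randomised. It reports from participant interviews that "there is a bias associated with the referral of patients to the clinics due to patient preferences and possibilities", giving family and work obligations and the ability to be away from home as reasons. It concedes that "we will not be able to eliminate the bias associated with differences in the referral of patients to the two clinics".

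The background section on modifiable and nonmodifiable factors names prognostic factors for RTW, among them "older age, lower educational level; lower socioeconomic status; and greater sick leave history". Table 3 shows that many candidate confounders are collected at enrolment. Data collection provides registry data from two years before inclusion.

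No propensity score, weighting or matching between the two clinics is described. The matched NAV group is an external treatment-as-usual comparator and does not adjust one clinic against the other.

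**The concern.** Waiting for an observed imbalance before adjusting belongs to a setting where imbalance arises by chance. Here it is expected, because patients and referrers choose the clinic for reasons plausibly linked to return to work.

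The rule has two weaknesses. First, the covariates depend on the observed data, so a real imbalance that does not show clearly enough stays in the estimate. Second, the power condition works backwards. The more strongly covariates separate the clinics, the more precision adjustment costs, so it is most likely to be dropped where confounding is greatest. The headline result is then the crude one.

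The consequences spread. The subgroup analyses use the same model as the primary outcome, and the economic evaluation goes ahead only if RTW rates differ significantly. The stated hypothesis is no overall difference, and confounding can hide a difference as easily as create one.

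**Working it through.** **Inputs from the article (Sample size).** 600 participants, 400 inpatient and 200 outpatient; about 50% with stable RTW at 1 year, so 0.5 × 600 = 300 events; two-sided 5%; 80% power at HR 0.73. |ln 0.73| = 0.315.

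**The plan's own figure.** Schoenfeld: power = Φ(√(events × a(1 − a)) × |ln HR| − 1.96), with a the share in one arm.
- At 2:1, a(1 − a) = 2/9: √(300 × 2/9) × 0.315 − 1.96 = 2.57 − 1.96 = 0.61, power 72.9%. For 80%, 357 events are needed.
- At 1:1, power is 77.8%.
- Other readings come close to 80%. Taking 50% as the outpatient rate with a higher inpatient rate gives 345 events and 78.7% at 2:1. Taking 50% in one arm and a higher rate in the other gives 334 events and 82.0% at 1:1. Follow-up to 5 years could also supply more events.

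The stated figure is therefore not called wrong here. What matters is that, on the plain reading, power is already short of 80%, so the power condition could be invoked.

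**How often a real imbalance shows (p < 0.05 assumed as the criterion).** True prevalence 50% (n = 400) against 40% (n = 200): pooled (200 + 80)/600 = 0.467; SE = √(0.467 × 0.533 × (1/400 + 1/200)) = 0.0432; 0.10/0.0432 = 2.31; Φ(2.31 − 1.96) = 64%. So it is missed about one time in three. If the factor has HR 0.70 for RTW (assumed), omitting it multiplies the clinic HR by about (0.5 × 0.7 + 0.5)/(0.4 × 0.7 + 0.6) = 0.85/0.88 = 0.966.

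**Several factors together.** Simulated Cox analyses: 400:200, 50% events, true clinic HR 1, independent binary factors with 40% prevalence in the outpatient arm and more in the inpatient arm, 600 runs per row. The conditional rule adjusts for a factor only if both its imbalance and its association with RTW have p < 0.05, and takes the power condition as met. Cells give average HR and type I error.

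| Assumed confounders | Crude | Conditional rule | Full adjustment |
|---|---|---|---|
| 4 factors, 8 points apart, HR 0.75 | 0.913; 12.8% | 0.960; 7.5% | 0.998; 4.7% |
| 4 factors, 10 points, HR 0.70 | 0.870; 22.8% | 0.967; 5.2% | 0.999; 5.8% |
| 6 factors, 6 points, HR 0.80 | 0.921; 11.5% | 0.948; 6.5% | 0.996; 4.5% |
| 3 factors, 5 points, HR 0.70 | 0.948; 8.3% | 0.970; 7.0% | 0.999; 6.7% |

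Monte Carlo error on a rejection rate near 5% is about 1 point. A repeat with another random seed gave average HRs within 0.01 of these, but single rejection rates moved by up to 3.5 points. The remaining bias under the conditional rule is clear; its type I error is not firmly separated from that of full adjustment. If the power condition fails, the crude column applies.

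**Cost of always adjusting.** Effective events = 300 × (1 − R²), where R² is the share of clinic membership explained by the covariates (assumed, as the article gives none). At 2:1 and HR 0.73:

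| R² | Power | Events needed for 80% |
|---|---|---|
| 0 | 72.9% | 357 |
| 0.10 | 68.4% | 397 |
| 0.20 | 63.2% | 447 |
| 0.30 | 57.5% | 511 |

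**The case against.** The article discloses the referral bias openly, and no adjustment removes its unmeasured part. Restricting adjustment to prognostic factors is defensible. Where screening works and power is judged sufficient, the remaining bias is modest. All of this stands, but disclosure is no reason to leave measured confounding in. A separate analysis plan could name covariates, but the conditional rule printed here would still need to be withdrawn.

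A reader might infer four stronger claims that the article does not support.

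- **Missed imbalances could equal the whole target effect.** A factor at 37% against 30% (200 against 400) has p = 0.084. With an assumed HR of 2 it shifts the log HR by ln(1.37/1.30) = 0.052, and six of these make 0.31, about |ln 0.73|. The number six is chosen to reach that total, and all six must favour one clinic and all escape detection. When this case is simulated with p < 0.05 as the trigger, about 2.5 of the six are flagged on average. The mean log HR is 0.26 crude and 0.11 under the rule, about a third of the target. Type I error is still 13%, so the case is not harmless, but it is extreme.
- **The baseline tests decide adjustment at p < 0.05.** The article does not link the two. That trigger is an assumption of the calculations above.
- **Reported p-values are invalidated.** Inflation depends on the scenario and ranges from negligible to material.
- **The aims flatly contradict the limitations.** The primary aim concerns differences in RTW success rates, whereas the limitation says "we will not be able to evaluate whether there are any significant differences in effect between the two interventions". A descriptive comparison with a causal disclaimer is a coherent reading. It sits awkwardly with a sample size justified by detecting a significant difference between the programs, so the wording needs reconciling.

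**Conclusion.** The rule is faulty as stated and should be changed. In a comparison with known referral bias, making adjustment depend on the observed data and on power can leave the main result crude or only partly adjusted for confounders that the study measures.

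In the four main scenarios the bias is modest if the power condition is met (HR 0.95 to 0.97 when the truth is 1). It is larger if that condition fails and the crude result stands (0.87 to 0.95, with type I error 8 to 23%). These sizes rest on assumed numbers, prevalences and strengths of confounders, all acting in one direction, and on an assumed p < 0.05 trigger. They show what the rule allows; they do not predict this study's bias. Full adjustment returns about 1.00 because every simulated confounder is measured. In the real study, unmeasured referral bias would remain.

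**What to change.** Delete the imbalance, correlation and power conditions. Make the primary clinic comparison an adjusted analysis with a covariate set fixed before the outcome data are examined, drawn from data already planned:

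- the prognostic factors that the article lists: age, education, socioeconomic status, prior sick leave from the two-year registry look-back, and employment and partial sick leave status at baseline;
- gender, diagnosis group, work ability and RTW expectation;
- the enrolment items that match the stated reasons for clinic choice: marital status, children, demanding caregiver tasks and family economy.

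The last group matters because a list of purely prognostic and work-related factors would miss much of the measurable part of the referral mechanism. Use outcome regression or a propensity-score method, chosen in advance. Report the crude result as supportive. Word the aim and the sample-size justification as an adjusted comparison subject to unmeasured referral bias, so that they agree with the limitations section.

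The cost is a change of wording, modest extra analysis and some precision. On the assumed R² values of 10% and 20%, power at HR 0.73 falls by about 5 and 10 percentage points (72.9% to 68.4% and 63.2%). That is the price of removing measured confounding and should be stated beside the sample size. No new data collection is needed.

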### Subgroup analyses

Subgroup analyses will be performed for the primary outcome (stable/sustainable RTW). All subgroup analyses will be performed using the same analytical model as that for the primary outcome but will also include the subgroup of interest and a treatment-by-subgroup interaction [69]. Interaction tests will be considered significant at the 5% level.

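### Program-by-subgroup tests in nonrandomised arms can pick up referral confounding as effect modification, because the adjustment is conditional and no confounder-by-subgroup terms are named

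*Protocol article*

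**What the plan says.** All references are to the protocol article.

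- **Model.** Outcome assessment and evaluation: "Cox proportional hazard models will be used to analyze the time until stable/sustainable RTW". Adjustment comes under a condition, "If there is an imbalance in any prognostic factors for RTW and this factor is strongly correlated with the RTW outcome", and then only subject to power: "analyses of differences in RTW between the two clinics will be adjusted for prognostic dissimilarities if we have sufficient power".
- **Subgroups.** Subgroup analyses: the tests are done "using the same analytical model as that for the primary outcome but will also include the subgroup of interest and a treatment-by-subgroup interaction". The decision rule is "Interaction tests will be considered significant at the 5% level". No other interaction term is named.
- **Allocation.** Limitations of the study says that "there is a bias associated with the referral of patients to the clinics due to patient preferences and possibilities" and that "we will not be able to eliminate the bias associated with differences in the referral of patients to the two clinics". It gives reasons, for example "Some prefer the outpatient program because they can ensure their ability to fulfill family or work obligations".
- **Use of the results.** The Aims hypothesise no overall difference but possible benefit of one or the other program in some subgroups (gender, age, job strain and others). The end of the Limitations section still intends to show differences between the clinics for different patient groups, and the only caution it gives there is about multiple testing. Impact of the study findings speaks of informing practice about for whom the interventions work.

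**The concern.** Under randomisation, a program-by-subgroup term isolates effect modification, because prognostic factors are balanced in expectation within every subgroup level. Without randomisation, the same term estimates true effect modification plus the difference in confounding between the levels. The stated reasons for choosing a clinic are family and work obligations. These could bear on RTW differently for, say, women and men.

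The entry rule adds a second difficulty. It asks whether a factor is strongly correlated with RTW, apparently in the whole sample. A factor that slows RTW in one level and speeds it in another can look weak overall and stay out of the model.

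The plan hypothesises no overall difference and looks to subgroups for one, so this is where a positive result is most likely to be reported. A correction for the number of tests would not help, because the bias sits in each single test. The referral-bias limitation is stated for the comparison of the two arms and is not carried over to the subgroup tests.

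**Working it through.** The documents give no figure for the interaction tests, so there is none to reproduce.

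**Inputs from the protocol (Sample size).** 200 outpatient and 400 inpatient participants; about 50% with stable RTW at 1 year, hence 600 × 0.50 = 300 events.

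**Assumed inputs (not in the documents).** One binary referral factor with prevalence p1 in the outpatient and p0 in the inpatient arm and hazard ratio g for RTW. There is no program effect in anyone.

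**Step 1: apparent program HR within one level if the factor is ignored.** Approximately (1 − p1 + p1·g) / (1 − p0 + p0·g). The spurious interaction is the ratio of this quantity between levels.

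- Opposite directions (50% vs 25%; g = 0.6 in women, 1.5 in men): women 0.80/0.90 = 0.889; men 1.25/1.125 = 1.111; ratio 0.80.
- Women only (60% vs 30% in women, g = 0.6; g = 1 in men): 0.76/0.88 = 0.864; ratio 0.86.
- Imbalance in one level only (65% vs 35%; balanced in the other), g = 2 in both: 1.65/1.35 = 1.22; ratio 1.22.
- Same imbalance and same g in both levels: 1.22/1.22 = 1.00. The interaction is not biased even without adjustment.

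**Step 2: rejection rate.** Var(log ratio) ≈ [1/(⅓ × ⅔)] × (1/d1 + 1/d2), with d1 and d2 the events in the two levels. With 60% women, 4.5 × (1/180 + 1/120) = 0.0625, so SE = 0.25. For a ratio of 0.80, |ln 0.80|/0.25 = 0.893, and Φ(0.893 − 1.96) + Φ(−0.893 − 1.96) = 0.145. The nominal 5% test rejects about 14.5% of the time. For 0.864 the same steps give about 9%.

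**Step 3: Cox simulations with and without adjustment.** These used 200:400, about 300 events, no program effect, and 350 to 1,500 studies per scenario. Ranges cover separate runs. Each cell shows the ratio of HRs and the rejection rate.

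| Factor | Unadjusted | Main effect | Plus factor-by-subgroup |
|---|---|---|---|
| Opposite directions (0.6 / 1.5) | 0.79–0.80; 14–16% | 0.79–0.80; 13.5–16% | 0.99–1.00; 4–6% |
| Women only (0.6 / 1) | 0.85–0.87; 8–10% | 0.88–0.90; 5.5–8% | 0.99–1.01; 5% |
| Imbalance in one level, g = 2 in both | 1.23; 13% | 1.00; 5.0% | 1.00; 5.5% |
| Same imbalance, g = 3 in one level only (65% vs 35%) | 1.39; 25% | 1.39; 24% | 1.01; 5.0% |

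With the factor acting in the same direction in both levels (0.6 and 0.8), main-effect adjustment gave 5.3 to 5.5%. Monte Carlo error at 600 studies and 15% rejection is √(0.15 × 0.85/600) = 1.5 percentage points.

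**Step 4: the entry rule.** In the opposite-direction scenario the factor's overall HR averaged 0.90 and reached p < 0.05 in only 12% of studies. A rule that asks for strong overall correlation would usually leave it out.

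**The case against.** A reader might infer that any referral bias differing between subgroups survives main-effect adjustment. It does not. With imbalance in one level only and an equally prognostic factor, adjusting for the main effect restored a ratio of 1.00 and 5.0% rejection. Other runs of that kind gave 0.98 to 0.99 and 3.5 to 6.1%.

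A reader might also infer that the plan misapplies a model belonging to randomised trials. The protocol does not describe it so, the source it cites for the method is not at hand, and a treatment-by-subgroup term is equally ordinary in observational work.

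Further points for the plan:

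- No passage says that family or work obligations affect RTW differently by gender, age or job strain. The opposite-direction case is an assumption, and in milder cases the inflation is hard to tell from simulation error.
- The article does not expressly confine covariates to main effects, and the detailed covariate form could sit in an analysis plan that is not shown.
- Referral bias is openly conceded for the two arms, false-positive subgroup findings are warned of, and several relevant baseline factors are collected.

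These points limit the size of the problem and rule out a claim that the subgroup results will be biased. They do not remove it. The article itself fixes the entry rule, the added terms and the 5% criterion, so the point does not rest on detail left to an analysis plan. The concession on referral bias stops short of the subgroup tests.

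**Conclusion.** The point holds in a conditional form. Confounding can pass for effect modification if a referral factor is kept out by the entry rule while its imbalance or its prognostic effect differs between levels. It can also do so if the factor enters as a main effect only while its prognostic effect differs between levels. Otherwise main-effect adjustment of a measured factor suffices.

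Under the assumed inputs, rejection after main-effect adjustment runs from about 5 to 6% in mild cases to about 15% for a factor acting in opposite directions. The 24% figure needs a hazard ratio of 3 in one level and none in the other. Omitting an equally prognostic factor that is imbalanced in one level only gave 13%. None of these inputs comes from the documents, so the figures show what is possible and do not predict what the study will find. They also assume the Cox analysis of stable RTW. The Primary outcome measures section bases subgroup evaluation on cumulative absence days instead, a separate inconsistency that should be settled.

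The change is worth making because subgroup differences are a main intended product of the study and the remedy is cheap.

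**What to change.** In Subgroup analyses:

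1. Fit every subgroup model with a pre-specified set of baseline confounders, included regardless of significance, observed imbalance or power. Candidates already collected are children, demanding caregiver tasks, family economy and work factors (appendix Table 3), and sick-leave history from the registry data covering 2 years before inclusion.
2. Add the products of the subgroup with those confounders, at least as a stated sensitivity analysis.
3. Show covariate balance between the clinics within each subgroup level.
4. Report interactions as exploratory associations, and state that the referral-bias limitation applies to them, because unmeasured preference cannot be adjusted away.

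Propensity weighting within each subgroup level is not asked for. It would split an outpatient arm of only 200 further, and its benefit is debatable.

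Cost: analysis wording only and no new data. The models carry more parameters. In simulation, the products widened the standard error of the interaction by about 3% for one confounder and 9% for ten.

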### Cost-effectiveness/utility/benefit analyses

In evaluating the cost-effectiveness/utility/benefit of the interventions, we will follow the Norwegian guidelines for health economic evaluation [71]. In performing the cost-effectiveness analysis (CEA) for the interventions, we will calculate a single combined measure, the incremental cost-effectiveness ratio (ICER). The ICER will be calculated as the difference in cost between the interventions divided by the difference in RTW outcomes. Second, the cost-utility analysis (CUA) will be performed with the SF-12 scores, which will be converted into SF-6D health utility scores as suggested by Brazier and colleagues [72]. The incremental cost-utility ratio will be calculated as the difference between costs for the interventions divided by the difference in the health utility, measured as quality-adjusted life years (QALYs). Any differences between the interventions will also be examined based on a cost-benefit analysis (CBA). In the CBA, the effects of the interventions, e.g., the QALYs and/or the intensity of labor market participation (stable RTW) and/or other health benefits, will be converted into Norwegian kroner.

